
### Aims

The primary objective of the study is the verification of the starting hypothesis that RAGT could have greater benefit, compared with conventional therapy alone, in gait speed improvement as assessed by the Timed 25-Foot Walk Test (T25FW).

Secondarily, the study aims to determine whether fatigue, QoL, balance and mobility are improved by RAGT. Finally, the study aims to collect information on whether RAGT or the active control group (CT) influence markers of plasticity, including clinical and circulating biomarkers, and if these modifications are correlated with clinical outcome. The ultimate goal is to draw tailored rehabilitation strategies capable of bypassing the person-specific treatment response in MS patients.

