### Secondary outcome measures

A significant number of secondary outcome measures will be employed to explore fatigue, QoL, balance, walking endurance, mobility and their possible connection with brain plasticity. Secondary outcomes will include: (1) clinical measures and questionnaires, (2) hemodynamic and metabolic evaluations and (3) laboratory-based measures. Every specific measure is detailed in the following section.

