#### Cerebral activation analysis during a motor task

The brain metabolism evaluation will be performed using another optical imaging system (NIRScout, NIRx Medical Technologies LLC, Glen Head, NY, USA) consisting of 16 light source fibers and 16 detector fibers, resulting in a 48-channel recording of cortical changes in oxygenated, deoxygenated and total hemoglobin. For the measurements of the present study the optodes will be tightly placed on the skull with the use of a holder cap with the interoptode distance set at 30 mm, covering the bilateral motor and premotor cortex. Patients will walk on the treadmill at a speed of 0.2 km/h assisted by personnel and with partial body weight support if needed, performing four short tasks (30 s of walking) alternated by rest periods (30 s) [73]. Data will be analyzed for possible selective changes of cerebral perfusion by specific software (NIRSlab). For each patient will be calculated the area under the curve of oxygenated, deoxygenated and total hemoglobin for each channel and hemisphere (media of the area under curve of each one of the 24 channels of selected hemisphere). Moreover, the data will also be analyzed with the software NIRS-SPM to draw a map of activation of the selected brain areas during the test and to perform a *t* test statistical comparison within subjects and between treatments, as well as other possible correlations with clinical or laboratory parameters.

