### Statistical analyses

Standard methods for the analysis of randomized controlled trials will be employed. Firstly a comparison of baseline characteristics of the two groups will be compared for demographics, primary and secondary outcome measures. Though our starting hypothesis called from a superiority of RAGT with respect to CT, to allow for the chance that participants enrolled in the CT group could have better outcomes than those in the intervention arm, we will use two-tailed tests of significance for all analyses. A *p* value of 0.05 will be considered statistically significant.

For the primary hypothesis, a two-way repeated measure analysis of variance (factors: treatment, time) will be run to compare differences in gait speed within the RAGT and CT groups at baseline, after treatment and follow-up. Given the large number of planned secondary outcomes, in order to reduce the probability of a false positive result, for these specific analyses the significance level will be fixed at 0.01.

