### Additional statistical analysis

The statistical significance of primary and secondary outcome measures in score change between the groups will be assessed using *t* tests for symmetrically distributed data and analogous nonparametric tests, such as the Wilcoxon signed-rank test, for data that are skewed. If a statistically different distribution between the two groups in the baseline outcome level is identified, a secondary analysis that employs a multivariate modeling, such as analysis of covariance, to adjust for these factors, will be performed. Since MS encompass a wide spectrum of disabilities, the general linear model will also analyze the effect of several factors, so we will conduct exploratory analyses in which we will include the MS onset (year) and EDSS subscores (pyramidal function, cerebellar function and sensitive functions) which define our MS in the model. Furthermore, the possible effects of disease-modifying or symptom-modifying drugs (i.e., fampridine) on motor outcome will be explored. Permutation tests may be implemented to verify that valid *p* values will be obtained even if model assumptions are not correct. Analysis of hemodynamic, metabolic and laboratory-based measures will be performed according to the procedures detailed above. Possible correlation between these factors and clinical measures will be assessed by Spearman’s rho or included in multiple regression models.

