## Discussion

The study may provide significant information on the rehabilitation of severely disabled, progressive MS patients, clarifying the possible application of technologies in clinical practice with a high number of participants with a limited range of disability; thus, reducing the bias present in the previous studies.

From the proposed trial, we expect to observe a greater effect of high-intensive robotic rehabilitation on mobility and functional recovery in a large cohort of MS patients compared to CT. Functional recovery after rehabilitation programs has to be considered a multifactorial process in which integrated and multicomponent biological systems are implicated, i.e., vascular, neuronal and metabolic. Quantity (duration and frequency) and quality (task-specificity) of interventions are appropriate to facilitate enhanced neural reorganization and motor recovery, favoring adaptations in the adult brain. Cortical adaptive changes could, therefore, contribute to functional recovery from lesions and may have an important role in compensating for axonal injury in MS. Therefore, following the intervention or during the different phases of intensive rehabilitation, we expect to detect possible modulation of biomarkers of brain plasticity related to cortical activation and/or of circulating regenerative markers, potentially correlated with the clinical outcomes. Our findings will help to identify specific markers to detect whether a patient should be a “responder” to a rehabilitative intervention, bearing in mind that due to a wide variety of symptoms, the rehabilitation process in persons with MS is multifactorial and should always be tailored to patient characteristics. Moreover, this study might increase knowledge on the effects of MS gait rehabilitation, leading to an optimization of health care resources and developing cost-effective rehabilitation programs. Lastly, from a scientific point of view, the study represents a step towards the knowledge of the functional reorganization processes in progressive MS patients, identifying the effectiveness of intensive rehabilitative interventions through the changes of clinical and circulating biomarkers of MS plasticity. However, further studies will be necessary to confirm the results related to the secondary outcomes.

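### Marker–outcome correlations are planned with Spearman's rho and no mention of randomised arm; adjusting the rank correlation for arm would keep a treatment difference from passing as a patient-level link

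*Protocol article*

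**What the plan says.** All references are to the protocol article.

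- **Aims** asks "whether RAGT or the active control group (CT) influence markers of plasticity", and then "if these modifications are correlated with clinical outcome". The primary hypothesis in the same section is that RAGT improves gait speed more than conventional therapy (CT).
- **Additional statistical analysis** gives the method for the hemodynamic, metabolic and laboratory factors: "Possible correlation between these factors and clinical measures will be assessed by" Spearman's "rho or included in multiple regression models". It does not say whether rho is computed over both arms, within each arm or adjusted for arm. It names no covariates for these regressions.
- **Cerebral activation analysis during a motor task** adds, for the cortical data, "as well as other possible correlations with clinical or laboratory parameters". It names no method for them.
- **Secondary outcome measures** places these markers among the secondary outcomes. **Statistical analyses** sets the general rule that a p "value of 0.05 will be considered statistically significant" and a stricter level of 0.01 for the secondary outcomes. All tests are two-sided.
- **Discussion** hopes to find markers that tell whether a patient will respond, and adds that "further studies will be necessary to confirm the results related to the secondary outcomes".

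**The concern.** Spearman's rho has no place for treatment arm. If one arm improves more in gait and also changes more in a marker, the patients form two shifted clouds. A rho across both clouds is then non-zero even when marker and gait are unrelated among patients given the same treatment. Both shifts are things the trial sets out to look for.

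The aim concerns whether a patient's marker change goes with that patient's recovery. The between-arm part of a pooled rho does not answer this. It repeats what the two arm comparisons, of gait and of the marker, already show. At stake is the reading of a secondary result: a marker of treatment received could be reported as a marker of recovery.

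**Working it through.** **Inputs from the article.** There are 98 patients, 49 per arm, allocated 1:1. The test levels are 0.05 and 0.01, two-sided. The only effect size is 0.40 (Sample size and power). It reproduces from the figures given there:

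(8.8 − 7.4) / √((3.1² + 3.8²)/2) = 1.4 / 3.47 = 0.40

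This is a change from baseline to end of treatment within RAGT. It is not a difference between RAGT and CT. The article gives no arm effect for any marker and no figure for the correlations, so the arm effects below are assumptions.

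**Induced correlation.** Let the outcome differ by d₁ SD and the marker by d₂ SD between arms, with zero correlation within arms. With 1:1 allocation the arm indicator has variance 1/4, so the pooled correlation is

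r = (d₁d₂/4) / √((1 + d₁²/4)(1 + d₂²/4))

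- Both 0.4: r = 0.04 / 1.04 = 0.038
- Both 0.6: r = 0.09 / 1.09 = 0.083
- Either one 0: r = 0

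**Approximate error rate.** Fisher's transformation shifts the test statistic by about r√(98 − 3).

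- Both 0.4: shift 0.038 × 9.75 ≈ 0.375. At 0.05: P(Z > 1.96 − 0.375) + P(Z < −1.96 − 0.375) = 0.056 + 0.010 ≈ 6.6%. At 0.01, with 2.576 in place of 1.96: 0.014 + 0.002 ≈ 1.6%.
- Both 0.6: shift ≈ 0.807. At 0.05: 0.125 + 0.003 ≈ 12.7%. At 0.01: 0.0384 + 0.0004 ≈ 3.9%.

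**Simulation.** This used 20,000 trials per setting, 49 per arm, and normal data with no association within arms. Pooled Spearman is compared with a rank correlation after removing the arm means of the ranks (98 − 3 = 95 df).

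| Arm effect, gait / marker (SD) | Mean pooled rho | Pooled: rejected at 0.05 / 0.01 | Arm-adjusted: rejected at 0.05 / 0.01 |
|---|---|---|---|
| 0.4 / 0 | 0.00 | 5.1% / 1.0% | 4.9% / 1.0% |
| 0.8 / 0 | 0.00 | 5.2% / 1.2% | 5.1% / 1.1% |
| 0.4 / 0.4 | 0.04 | 6.8% / 1.6% | 5.3% / 1.0% |
| 0.4 / 0.8 | 0.07 | 10.7% / 3.1% | 5.0% / 1.0% |
| 0.4 / 1.0 | 0.09 | 13.6% / 4.1% | 5.1% / 1.0% |
| 0.6 / 0.6 | 0.08 | 12.3% / 3.7% | 4.7% / 0.9% |
| 0.6 / 1.0 | 0.13 | 24.6% / 9.6% | 5.2% / 1.1% |

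Repeat runs gave 6.5% for 0.4/0.4 and 12.5–12.9% for 0.6/0.6 at 0.05, in line with the approximation. With 44 per arm (the 88 before allowance for dropout), the rates were 6.4% / 1.5% for 0.4/0.4 and 11.9% / 3.5% for 0.6/0.6.

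**The case against.** The strongest reply is that the article does not say the arms are pooled. It is silent, it condenses a fuller protocol, and an analysis plan may specify the detail. The same sentence also names multiple regression, which can carry an arm term. This stands in part. Pooling is an inference, and the lack of a covariate list for the regressions is ordinary detail left elsewhere, not a fault. What remains is that the first-named method cannot take account of arm in its plain form, and a form that can is available at almost no cost.

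A reader might infer something stronger: that if RAGT works, markers unrelated to recovery will be declared correlated with it, and more of them the better RAGT works. The document does not support that, for two reasons.

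- A gait effect alone is not enough. With no marker difference between arms the error rate stays nominal, even at a gait effect of 0.8 SD.
- Even with both effects present, most unrelated markers would not be declared. In the table, at least 75% are not declared at 0.05 and at least 90% are not declared at 0.01.

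Three further points limit the size, and all stand. The larger rates need arm effects that the article does not give, and CT is itself active walking training. The markers are secondary outcomes, so 0.01 is arguably the relevant level. The planned wording also covers associations at baseline, where randomisation leaves no systematic arm difference. Finally, the article itself says that secondary results need confirmation.

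**Conclusion.** The point holds as a minor one. On the natural reading, the planned rho mixes a between-arm component into an association meant to be about patients, provided that arm shifts both variables. With both effects at 0.4 SD the inflation is slight: about 6.5–7% instead of 5%, and 1.5% instead of 1%. With both at 0.6 SD it is about 12–13% and 4%. Without a marker difference by arm there is none.

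This rests on three assumptions: that rho is computed over both arms, that the arm effects have the sizes used, and that the data are normal within arms. The primary comparison, the sample size and the conduct of the trial are not affected.

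**What to change.** In Additional statistical analysis, state that the rank correlation between marker and clinical outcome is a partial Spearman correlation adjusted for randomised arm, with the within-arm rho values shown beside it. State also that randomised arm is included when the multiple regression route is used. Apply the same wording to the correlations foreseen for the cerebral activation data.

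The cost is one or two sentences and one degree of freedom (95 instead of 96 with 98 patients). No new data are needed. In the simulated settings the adjustment brings the error rate back to 4.7–5.3% at 0.05 and 0.9–1.1% at 0.01.

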### Intention-to-treat

All analyses will be conducted using intention-to-treat, where any subject randomized to one arm remains in that arm regardless of whether or not they received the intervention. Missing values, though we will make any effort possible to reduce their incidence, will be treated using the multiple imputation procedure, considered one of the best methods to handle missing data [83]. Moreover, a sensitivity analysis that assesses the stability of the study’s conclusions, comparing intention-to-treat analysis to an analysis that takes into account level of participation in the intervention arm, will also be performed.

### Data monitoring and interim analysis

The RAGTIME trial, dealing with well-established and safe rehabilitation procedures, paralleled by a rigorous handling of potential harms as a local hospital policy, expects to minimize all the potential risks. Moreover, this being a single-center study, a Data Monitoring Committee will not be required. The research coordinator will be in charge of the interim analysis (with statistician support) and for taking the final decision to stop, modify or terminate the trial. Eventual possible modifications or amendments to the protocol will be discussed within the research group and communicated by the research coordinator to the funding body for approval or refusal. An interim analyses performed by the scientific experts of the funding body will be scheduled after 18 months from the beginning of the trial. It will consist of a compilation of an interim evaluation checklist form, of a study interim report form and a public preliminary data presentation and discussion. Once the trial is concluded, the research coordinator will be responsible for the final dataset, and will state the number of research team members who can have access to the data collected.

### Dissemination plan

The results derived from this trial will be published in high-quality journals and presented at national and international meetings. The results will also be disseminated through conferences organized by the funding agency, Regione Emilia Romagna. The authors also intend to spread the information learned from this project by presenting it at MS support groups, to inform the patients about the efficacy of one or the other treatment and the local availability of them.

## Discussion

The study may provide significant information on the rehabilitation of severely disabled, progressive MS patients, clarifying the possible application of technologies in clinical practice with a high number of participants with a limited range of disability; thus, reducing the bias present in the previous studies.

From the proposed trial, we expect to observe a greater effect of high-intensive robotic rehabilitation on mobility and functional recovery in a large cohort of MS patients compared to CT. Functional recovery after rehabilitation programs has to be considered a multifactorial process in which integrated and multicomponent biological systems are implicated, i.e., vascular, neuronal and metabolic. Quantity (duration and frequency) and quality (task-specificity) of interventions are appropriate to facilitate enhanced neural reorganization and motor recovery, favoring adaptations in the adult brain. Cortical adaptive changes could, therefore, contribute to functional recovery from lesions and may have an important role in compensating for axonal injury in MS. Therefore, following the intervention or during the different phases of intensive rehabilitation, we expect to detect possible modulation of biomarkers of brain plasticity related to cortical activation and/or of circulating regenerative markers, potentially correlated with the clinical outcomes. Our findings will help to identify specific markers to detect whether a patient should be a “responder” to a rehabilitative intervention, bearing in mind that due to a wide variety of symptoms, the rehabilitation process in persons with MS is multifactorial and should always be tailored to patient characteristics. Moreover, this study might increase knowledge on the effects of MS gait rehabilitation, leading to an optimization of health care resources and developing cost-effective rehabilitation programs. Lastly, from a scientific point of view, the study represents a step towards the knowledge of the functional reorganization processes in progressive MS patients, identifying the effectiveness of intensive rehabilitative interventions through the changes of clinical and circulating biomarkers of MS plasticity. However, further studies will be necessary to confirm the results related to the secondary outcomes.

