### Intervention

Participants in both intervention groups will receive twelve 2-h training sessions over a 4-week period, resulting in a three sessions/week pattern. A pragmatic window will be set to ensure for each participant the execution of all 12 sessions in a maximum of 5 weeks, to accommodate possible withdrawal of one or more sessions (e.g., intercurrent illness, sudden family problems, etc.). Patients who miss more than three consecutive training sessions will be dropped out from the study. If a participant misses a training session, the physiotherapist will inform the research coordinator and will contact the patient by phone, to determine reasons for missing and to motivate them to take part to the next scheduled training session.

The first training hour will consist of the specific training scheduled for each group (gait training), whereas the second training hour will be common to both groups. In detail, an experienced physiotherapist will perform lower-limb and core stretching exercises to increase muscle flexibility as well as strengthening exercise for the lower limbs. The second training hour will be carried out over the entire duration of the study by the same physiotherapist, treating two participants contemporaneously, to ensure the same exercises for all patients to avoid possible confounding factors and bias during the results interpretation.

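### The responder and tailoring goal has no matching analysis, and marker changes common to two trained arms cannot be credited to training

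*Protocol article*

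**What the plan says.** The Aims section of the protocol article asks whether the training given in either arm will "influence markers of plasticity, including clinical and circulating biomarkers, and if these modifications are correlated with clinical outcome". It then adds: "The ultimate goal is to draw tailored rehabilitation strategies capable of bypassing the person-specific treatment response in MS patients". The Discussion goes further. It expects to "help to identify specific markers to detect whether a patient should be a" responder to a rehabilitative intervention, and it describes the study as "identifying the effectiveness of intensive rehabilitative interventions through the changes of clinical and circulating biomarkers of MS plasticity".

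The analyses that bear on this are spread over several sections:

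- *Secondary outcome measures* classes the hemodynamic, metabolic and laboratory measures as secondary outcomes.
- *Additional statistical analysis* tests score change in primary and secondary outcomes between the groups. Analysis of covariance follows only if the baseline levels differ statistically.
- *Cerebral activation analysis during a motor task* plans comparisons both within patients and across treatments.
- On the link with outcome, *Additional statistical analysis* states: "Possible correlation between these factors and clinical measures will be assessed by" Spearman's rho or by inclusion in multiple regression models. The factors it names for exploratory modelling are MS onset, EDSS subscores and drug treatment. It names no baseline marker and no term with arm.

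Under *Intervention*, both arms receive twelve two-hour sessions, and "the second training hour will be common to both groups". There is no untrained arm.

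**The concern.** Two claims go beyond what the stated design and analyses can deliver.

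The first is the responder claim. To pick patients for a treatment, the marker must be known before treatment. To choose between two treatments, its relation to outcome must differ between them. The question stated in the Aims is about marker modifications, which exist only after training has begun. Even the intermediate visit comes after six of the twelve sessions.

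The second is the reading of effectiveness from marker changes. All patients train, half of each session is identical in both arms, and patients enter after three months without rehabilitation (an exclusion criterion). A change seen in both arms may come from the specific training, the shared hour, general reconditioning, repeat testing or natural course.

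At stake is a report that a marker identifies responders, or shows that training works, based on associations that would look the same if the robot had no specific effect.

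**Working it through.** **Inputs.** 88 evaluable patients, so 44 per arm, and 98 randomised, so 49 per arm (*Sample size and power*). Two-sided tests, with 0.01 for secondary outcomes (*Statistical analyses*). The article gives no marker effect size, drift or correlation, so those below are assumptions.

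**The plan's own figure.** It gives none for the markers. For the primary outcome, the dropout step reproduces: 88/0.9 = 97.8, rounded up to 98. The 88 itself does not follow from an effect size of 0.40 in a two-sided two-sample comparison, which gives 99 per arm (198). That is a separate matter, and 88 serves here only as the planned evaluable number.

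**Step 1: what a marker change identifies.** Write the mean change as s + h + r in RAGT and s + h + c in CT. Here s is drift (time, repeat testing, natural course), h the shared hour, and r and c the arm-specific training.

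- Between arms: (s + h + r) - (s + h + c) = r - c. Randomisation protects this, and it answers RAGT versus CT.
- Within an arm: s + h + r (or c). If h = r = c = 0, the change is s alone.

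Suppose s is 0.5 SD of the change score (assumed), no training has any effect, and n = 44. The chance of a significant within-arm change at 0.01 is Φ(0.5 × √44 - 2.576) = Φ(0.741) = 77%. With s = 0.3 SD it is Φ(1.990 - 2.576) = Φ(-0.586) = 28%.

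**Step 2: what a marker-outcome association identifies.** Let outcome = a + b·arm + c·M + d·arm·M, with M the baseline marker. The slope on M is c in CT and c + d in RAGT. Choosing RAGT over CT by marker requires d. With a correlation of 0.4 in both arms (assumed, equal SDs), d = 0 and the marker says nothing about which treatment to give. With no untrained arm, c also mixes prognosis with response to training. So even a responder to rehabilitation in general is not identified.

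**Step 3: what an interaction test could detect.** For 80% power at two-sided 0.01 the multiplier is 2.576 + 0.842 = 3.417 (from unrounded values).

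| Quantity | Formula | 44 per arm |
|---|---|---|
| Fisher-z difference | 3.417 × √(2/41) = 3.417 × 0.2209 | 0.755 |
| Symmetric example | tanh(0.755/2) | +0.36 versus -0.36 |
| Slope difference, outcome SD per marker SD | 3.417 × √(2/44) = 3.417 × 0.2132 | 0.73 |
| Power for a slope difference of 0.40 (assumed) | Φ(0.40/0.2132 - 2.576) = Φ(-0.700) | 24% |

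The most lenient setting, 5% with all 49 per arm, still needs 2.80 × √(2/46) = 0.584 in Fisher z (about +0.28 versus -0.28). For a slope difference it needs 2.80 × √(2/49) = 0.57.

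**Step 4: the between-arm marker comparison.** At 0.01 with 44 per arm, the smallest difference detectable with 80% power is also 0.73 SD of the quantity analysed. If ρ is the baseline-to-follow-up correlation, the variance is proportional to 2(1 - ρ) for a change score and 1 - ρ² for a baseline-adjusted analysis. The ratio of adjusted to change-score variance is (1 + ρ)/2: 0.65, 0.75 and 0.85 for assumed ρ of 0.3, 0.5 and 0.7. Adjustment gains precision whether or not the baselines differ.

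**The case against.** The strongest reply is that the marker aims already have a randomised analysis. Markers are secondary outcomes, change in secondary outcomes is tested between the groups, and cortical activation is compared across treatments. **This stands.** A reader might infer from the Aims and Discussion that the marker work rests on within-arm changes alone, but the document does not support that. One weakness remains: the nonparametric test named for skewed data is the signed-rank test, a paired test that does not compare two independent arms.

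Second, the Discussion speaks of response to a rehabilitative intervention, not to RAGT. That is correct, and the article nowhere promises a marker for choosing RAGT over CT in those words. The general tailoring goal in the Aims invites that use, however, and the broader reading is not identified either (Step 2).

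Third, the regression models are left open. They could include T0 values, arm and an interaction, and an analysis plan that is not shown may say so. It would therefore be wrong to infer that the arms will be pooled or that opposite correlations will cancel unseen, since no pooling rule is stated. But the article itself states both the promise and the analysis meant to serve it, and the two do not match.

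Fourth, the language is often cautious, and the Discussion says that secondary results need confirmation. That moderates the concern, but repeating the same correlation would not answer the question.

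Fifth, an active comparator is a legitimate choice for the primary question. Agreed: it only limits what changes common to both arms can show.

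**Conclusion.** The concern holds in limited form. The trial can show whether RAGT moves a marker differently from CT. It cannot attribute to training a marker change seen in both arms, so the Discussion should not read effectiveness from such changes. The responder and tailoring goal has no stated analysis that could support it.

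A reader might conclude that the trial cannot show any training effect on a marker. That is true only of training versus no training. Nor can an interaction test be treated as decisive. At the plan's 0.01 level with 44 per arm, it reliably finds only a large effect: a Fisher-z difference of about 0.755, or 0.73 outcome SD per marker SD.

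These sizes rest on normal approximations, on 44 evaluable patients per arm, and on applying the secondary-outcome level to the marker models. The drift and 0.40 examples are illustrations, not estimates from the article.

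**What to change.** (a) In *Additional statistical analysis*, make the between-arm difference in marker level at T2 (and T3), adjusted for T0, the stated analysis of marker effects. It replaces the unadjusted change-score test with covariance adjustment only when baselines differ. For skewed markers, transform or use a test for independent groups. Label within-arm changes and correlations of change with change as descriptive.

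(b) For a short list of markers named in advance, add an exploratory model of T2 T25FW on arm, baseline T25FW, T0 marker and arm-by-T0-marker. Report the interaction with its confidence interval.

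(c) In the *Discussion*, describe the marker results as hypothesis-generating. Do not say that any marker guides the choice of RAGT over CT without an interaction, and do not infer effectiveness from changes common to both arms.

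The cost is wording plus a few models. No new data are needed, because blood is already drawn at T0 and at every later visit. The downside is more modest claims and an interaction test that is openly low-powered.
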